## Abstract

**Background:**

Hyperuricemia (HUA) is a metabolic disease by purine metabolism disorders. It is a risk factor for many chronic diseases, including diabetes, hypertension, and heart disease. Studies have shown that exercise can effectively reduce serum uric acid (SUA), but the optimal exercise dose, intensity, and mode of exercise for improving HUA have not been verified in clinical studies. Therefore, this study aims to explore the effect of different exercise intensities in improving SUA of patients with HUA.

**Methods and Analysis:**

A randomized, single-blind, parallel controlled trial will be conducted in this study. 186 HUA patients who meet the inclusion criteria will be randomly divided into a 1:1:1 ratio (1): control group (2), low-intensity exercise group (brisk walking, 57-63% maximum heart rate, 150 min/week, 12 months), and (3) moderate-intensity exercise group (jogging, 64-76% maximum heart rate, 150 min/week, 12 months). The three groups of subjects will receive the same health education and prohibition of high-purine diet during the intervention period. The primary outcomes will be SUA concentration, SUA concentration change (mg/dL), SUA change rate (%), and the proportion of HUA patients. Secondary outcomes will include anthropometric parameters (body weight, waist circumference, hip circumference, BMI); physiological indicators (blood pressure, grip, vital capacity, maximum oxygen); biochemical indicators (blood lipid, blood sugar, liver enzyme, creatinine, and blood urea nitrogen). Each group of patients will go through an assessment at baseline, 3rd, 6th, and 12th months.

**Discussion:**

This study will evaluate the effect of 12-month low-intensity exercise and moderate-intensity exercise on HUA patients. We hypothesize that both low-intensity and moderate-intensity exercise would improve HUA as compared with no-exercise control, and that moderate-intensity exercise would be more effective than low-intensity exercise in improving HUA. These results can provide a basis for the current physical activity guidelines for HUA’s healthy lifestyle management.

**Ethics and Dissemination:**

This study has been approved by the Ethical Review Committee of the Shanghai University of Sport (approval number: 102772020RT005). Informed consent will be obtained from all participants or their guardians. The authors intend to submit the study findings to peer-reviewed journals or academic conferences to be published.

**Clinical Trial Registration:**

Chinese Clinical Trial Registry, identifier ChiCTR2100042643.

## Background

Hyperuricemia (HUA) is a metabolic disease caused by the disorder of purine metabolism, which results in increased production or decreased excretion of serum uric acid (SUA) (1). HUA is defined as under a normal purine diet, the SUA level of two fasting tests on different days, male>7mg/dL, female>6mg/dL (2–4). According to statistics, the number of HUA in China has reached 170 million, and the overall prevalence rate is 13.3% (5). In recent years, the incidence of HUA is on the rise, showing a trend in younger age (5). HUA patients aggravate with the increase of SUA levels, often leading to the occurrence of gout. At present, there are more than 80 million gout patients in China, and it is increasing rapidly at an annual growth rate of 9.7% (5). In addition, HUA is a risk factor for many chronic diseases. When the SUA level increases by 60 μmol/L, the incidence of diabetes increases by 17% (6), the incidence of hypertension increases by 13% (7), and the risk of death from coronary heart disease increases by 12% (8).

The symptoms of HUA are not obvious, which cause delay in treatment. The current management of HUA mainly includes medication and lifestyle adjustments. Xanthine oxidase inhibitors are often used as first-line drugs for HUA, including allopurinol (9) and febuxostat (10, 11). However, the side effects caused by long-term drug use, such as severe skin reactions, renal toxicity, need to be paid attention to (12–14). In addition, HUA patients can reduce SUA by adjusting lifestyles. Studies have shown that a healthy lifestyle including dietary regulation, restriction of tobacco and alcohol, regular exercise, and weight control can reduce SUA concentration by 10%-18% or 70-90mol/L (15–17). A multi-center longitudinal study (18) showed that HUA patients who do not exercise for (<1 hour/week) their mortality increases by 27%, of which life expectancy is shortened by 4.3 years in male, and 5.7 years in female. While HUA patients who exercise for (≥7.5MET/hour/week) mortality reduces by 11%, hence life expectancy is extended by 4-6 years, which shows that adequate exercise can reduce the risk of death and extend life. In addition, a Korean cohort study (4) showed that subjects who were sedentary for ≥10 hours a day were more likely to develop HUA than subjects who were sedentary for <5 hours a day. However, several small clinical trials have found that physical exercise does not have a positive effect on SUA levels (19–22). At present, there is no uniform standard for exercise dose and intensity to prevent or treat HUA (23–25). In addition, the long-term effects of exercise therapy have not been confirmed, and need to be verified in future clinical studies.

In this study, our purpose is to explore the effect of different exercise intensities in improving SUA of patients with HUA. We will conduct a 12-month randomized controlled trial to determine the impact of low-intensity exercise and moderate-intensity exercise on HUA. We hypothesize that both low-intensity and moderate-intensity exercise can improve HUA, and that moderate-intensity exercise is more effective than low-intensity exercise in improving HUA.

## Materials And Methods

### Research Design

This study is a single-blind, multi-center, parallel randomized controlled trial. Recruitment starts in July 2021 and ends in July 2022. The study period (including the one-year recruitment period) is 3 years. Participants will be randomly divided into a control group, a low-intensity exercise group, and a moderate-intensity exercise group. Tests will be performed at baseline, 3rd, 6th, and 12th months. The research flowchart is shown in **Figure 1**. This study has been ethically approved by the Ethical Review Committee of Shanghai University of Sport (approval number: 102772020RT005, Chinese clinical trial registration: ChiCTR2100042643). All patients should provide written informed consent before enrollment. The study will be following the Guidelines of Comprehensive Reporting Test Standard (CONSORT) (26).

**Figure 1 f1:**
[figure not shown]
Trail flow chart.

### Research Setting

This study will recruit 186 eligible subjects from multiple medical institutions, such as Zhongshan Hospital with Fudan University, Huashan Hospital Affiliated with Fudan University, Yangpu District Shidong Hospital, Yinhang Community Health Service Center. All research diagnosis and blood index tests will be carried out in the Zhongshan Hospital with Fudan University. Exercise intervention, anthropometric parameters and physiological indicators will be completed in Shanghai University of Sport.

### Inclusion Criteria

(1) Men and women;(2) Age: 45-60 years old;(3) Diagnose with HUA, within 4 weeks. Under normal purine diet, two fasting tests on different days, SUA>7mg/dL (male), SUA>6mg/dL(female);(4) No history of gout;(5) Agree and sign the informed consent form.

### Exclusion Criteria

(1) Use drugs that may affect uric acid within 1 month before enrollment, including benzbromarone, allopurinol, febuxostat, etc;(2) Psychiatric conditions;(3) Serious medical diseases, such as cancer, angina pectoris, cerebral infarction;(4) Participated in other clinical trials in the past 4 weeks.

### Randomized Allocation and Blinding

After the baseline assessment, the study will use a 1:1:1 ratio to randomly divide the subjects into 3 groups. The random table will be provided by the Statistics Department of the School of Public Health, Fudan University (Excel software; Microsoft). The test will be completed by unrelated personnel, and the random table will be kept by the main investigator. The researcher will conceal the distribution in an opaque envelope, which can only be opened after the subject has completed the baseline assessment. At the same time, this study is a single-blind randomized trial. In this study, all subjects will be unaware of the allocation of the control group, low-intensity exercise group, and moderate-intensity exercise group. The concentration of uric acid in serum and urine will be measured in Zhongshan Hospital affiliated with Fudan University. The measured values of SUA will be hidden from the investigator and patient to maintain a blind assignment.

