### Intervention

#### Control Group

The subjects in the control group will be given health education and maintain their original lifestyle. Control subjects will be given a monthly uric acid popular science lecture, such as the relationship between hyperuricemia and gout, diet control of hyperuricemia patients, and correction of poor lifestyles. During the study period, high-purine diets will be banned.

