#### Moderate-Intensity Exercise Group

Participants in moderate-intensity exercise group will be intervened at Shanghai University of Sport at 64-76% of maximum heart rate (220 - age) (17). The exercise frequency will be 30 minutes a day, 5 days a week, for a period of 12 months. The subject will wear a heart rate monitor during exercise to monitor exercise intensity. In the first 2-4 weeks, subjects will exercise for 15-30 minutes at 57-63% of their maximum heart rate. Then, the exercise intensity of the subjects will gradually increase to 64-76% of the maximum heart rate, and the time will be increased to 30 minutes. In addition, the moderate -intensity exercise group will maintain the same health education and prohibition of high-purine diet as the control group.

In the low-intensity exercise group and the moderate-intensity exercise group, all exercise sessions will be supervised by research staff. The exercise intensity, duration, heart rate and blood pressure before and after exercise, and adverse events during exercise will be recorded by study staff. The study participant retention is critically important and every effort will be made to increase participants’ adherence to their intervention and follow-up visit schedule. If the subject fails to participate in the study more than 3 times in a row, the researcher will call the subject to ask the reason and encourage the subject to continue participating in the study. During the research process, the researchers will also send personalized gifts to the participants to strengthen their enthusiasm.

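### The single blind is defined as participants not knowing their arm, which the protocol's own description of the three arms rules out

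*Protocol article*

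**What the plan says.** Under Randomized Allocation and Blinding, the protocol article gives the level of blinding, "At the same time, this study is a single-blind randomized trial", and then the party to whom it applies: "all subjects will be unaware of the allocation of the control group, low-intensity exercise group, and moderate-intensity exercise group". The same section describes one supporting measure: "The measured values of SUA will be hidden from the investigator and patient to maintain a blind assignment".

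It also contains a sentence that may or may not concern outcome assessment: "The test will be completed by unrelated personnel, and the random table will be kept by the main investigator".

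On the arms, the Control Group section says: "Control subjects will be given a monthly uric acid popular science lecture". These participants otherwise continue their usual life. The two exercise sections prescribe 30 minutes a day, five days a week, for 12 months, at a university site and with a heart-rate monitor worn, and add that "all exercise sessions will be supervised by research staff". The abstract names the activities. It describes one arm as "low-intensity exercise group (brisk walking, 57-63% maximum heart rate, 150 min/week, 12 months", and the other as jogging at 64-76% of maximum heart rate.

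On assessment, Outcome Assessment refers to assessors without saying what they know. Research Setting adds: "Exercise intervention, anthropometric parameters and physiological indicators will be completed in Shanghai University of Sport".

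**The concern.** Participants can be blinded to allocation only if the arms look alike to them. A lecture once a month and a year of supervised exercise do not look alike, and no sham or attention-matched activity is described. The stated blind therefore appears to be one the trial cannot have.

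Two things are at stake. First, the single-blind label stands in the abstract, in Research Design and in the blinding section. It would pass into the trial report as protection against participant-driven bias that does not exist. Participants who know their arm may change their diet or outside activity, or drop out at different rates. The Discussion concedes that purine intake is not strictly controlled, so there is a behavioural route to SUA itself.

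Second, by assigning its single blind to the one party that cannot be blinded, the article leaves undefined the blinding that is feasible, that of laboratory staff and outcome assessors. Grip, vital capacity and maximum oxygen depend on effort and encouragement, and waist circumference depends on the operator. For these, an assessor's knowledge of the arm could matter.

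**Working it through.** No figure in the plan bears on this point, so the check sets the blinding text against the rest of the article.

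1. **Control versus exercise.** A control participant is offered one lecture a month, about 12 in the year. An exercise participant is scheduled for 5 sessions × 52 weeks = 260 supervised sessions in the year. By sample size, 62 participants are planned for control and 2 × 62 = 124 for the exercise arms, 186 in all. Everyone can tell which of these two conditions they are in from the first weeks.

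2. **Low versus moderate intensity.** Both exercise arms share the schedule, the site, the monitor and the gradual start. They differ in activity (brisk walking or jogging, according to the abstract and the Discussion) and in heart-rate band. With maximum heart rate taken as 220 minus age, as the article does, a participant aged 45 has 220 − 45 = 175 beats/min:
   - low band: 0.57 × 175 = 99.8 to 0.63 × 175 = 110.3;
   - moderate band: 0.64 × 175 = 112.0 to 0.76 × 175 = 133.0.

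   At age 60 the maximum is 160 beats/min, and the bands are 91.2 to 100.8 and 102.4 to 121.6. The bands do not overlap after the run-in of 2 to 4 weeks, and the participant wears the device that measures them. A participant may not know the label attached to the arm, but will very likely know whether the task is to walk or to jog.

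3. **The stated mechanism.** Withholding SUA results stops a participant or investigator from reacting to a result. It does not remove knowledge of the treatment received, so it cannot maintain a blind that step 1 shows to be absent.

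4. **The limitations.** The Discussion expects the counselling-only control to dampen enthusiasm and hamper recruitment. That fits participants knowing what they receive, but recruitment difficulty could explain it too, so it is only weak support. Unblinded participants are not among the limitations listed.

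5. **Assessors.** The article says where the physical measurements are made, not by whom relative to the exercise supervisors, and not whether those people know the arm. The sentence on unrelated personnel shares its full stop with a statement about the random table, so the test it mentions may be outcome testing or the handling of randomization. On either reading, being unrelated to the study is not the same as being unaware of allocation. The text neither establishes nor excludes assessor blinding.

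**The case against.** The strongest objections concern how far the point reaches.

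- **Assessors.** A reader might infer that no assessor is blinded, or that the staff who supervise exercise also take the measurements. The documents do not support either inference. A condensed article commonly leaves assessor masking to the full protocol, a shared site is not shared staff, and the wording on unrelated personnel could refer to independent testers. This objection stands: assessor blinding is something to secure, not an error to correct.

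- **The primary outcome.** A reader might infer that measurement of SUA is compromised. It is a laboratory value, assayed at a hospital separate from the exercise site, with results withheld from investigator and patient, and nothing suggests that the laboratory learns the arm. This stands too. What remains for SUA is behavioural, and it is partly limited because all three arms receive the same health education and the same ban on high-purine food. Awareness of this kind is inherent in comparing exercise with no exercise, and no rewording removes it.

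- **Between the exercise arms.** The intervention sections describe the two programmes by heart-rate band alone, and nothing says that participants are told their zone. Ignorance of the low or moderate label is conceivable. This stands in part: awareness is certain for control against exercise, and very likely, not certain, for walking against jogging.

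- **The label.** A trial with blinded assessors may still be called single-blind, so the term need not be withdrawn. This stands.

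None of these objections rescues the sentence itself. The article makes a positive statement that participants are unaware of all three allocations, and further detail in a fuller document could not make that true.

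**Conclusion.** The point holds in this form: the definition of the single blind contradicts the arms as described, and should be corrected. It affects all 186 planned participants for control against exercise, and very probably the 124 in the exercise arms for walking against jogging. The first statement rests only on the article's account of the arms; the second also assumes that the activities named in the abstract are those delivered.

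The documents give no basis for estimating a bias, and none is claimed. The correction removes a false safeguard from the record but leaves participants' awareness where it is. The accompanying request, to state and arrange blinding of laboratory staff and assessors, protects mainly grip, vital capacity, maximum oxygen and waist; the gain for SUA is small. The article does not show that these assessors are unblinded.

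**What to change.** Replace the sentence on participants in Randomized Allocation and Blinding with a statement to this effect: *participants and exercise supervisors are not blinded. The single blind applies to laboratory staff, who receive samples labelled by study number only, and to the assessors of anthropometric and physiological outcomes, who do not supervise exercise sessions and are not told the arm.* Withholding SUA results can stay as a separate measure, without the claim that it keeps the assignment blind.

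In the same section, say which test the unrelated personnel carry out. Keep the term single-blind in the abstract and in Research Design only with the meaning above. Add unblinded participants to the limitations in the Discussion.

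The cost is a less favourable, but true, description of the blinding, and rostering so that existing staff who supervise sessions do not also assess. The documents give no staffing figures, so this assumes that staffing allows the separation; if it does not, the text should claim blinding only for those who are in fact blinded. Arms, sample size and visit schedule do not change. Trial Status puts the study before recruitment, so the arrangement can be in place for the first participant.

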### Sample Size Calculation

According to the existing literature (27), after 45 days of short-term moderate-intensity aerobic exercise intervention in patients with HUA, the average improvement value of SUA was 48.8 µmol/L (0.82 mg/dL). This study will carry out a long-term exercise intervention (12 months) in 3 groups. Test power (1-β) is set at 0.80; significance level (α) is set at 0.05. The sample size is estimated using the F test in G*Power (version 3.1.2, Franz Paul, Universit Kiel, Germany). After calculation, the total sample size is 159 cases, with 53 cases in each group. Taking into account the loss to follow-up, the total sample size in the actual study requires 186 subjects based on a 15% loss to follow-up rate. Therefore, at least 62 subjects are included in each group.

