#### Mathematical Statistics

The data collected in the experiment will be statistically analyzed by SPSS 25.0, and the results will be expressed in the form of mean ± standard deviation. According to the specific values of each index, the Kolmogorov-Sminov test is used to determine whether it conforms to the normal distribution. If the index conforms to the normal distribution, the independent sample T-test is used to judge the difference between the two groups, and the paired sample T-test is used to judge the difference between each group before and after the intervention. If the index does not conform to the normal distribution, the Mann-Whitney test in the non-parametric test is used to judge the difference between the two groups, and the Wilcoxon test is used to judge the difference before and after the intervention in each group. Spearman correlation analysis is used to test the correlation of each index. P= 0-0.05 is set as the significance level.

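### The 80% power is for an F test that the listed analysis does not contain, and it does not carry over to the pairwise hypotheses, least of all to moderate versus low intensity

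*Protocol article*

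**What the plan says.** Sample Size Calculation fixes the error rates ("Test power (1-β) is set at 0.80; significance level (α) is set at 0.05") and names the method: "The sample size is estimated using the F test in G*Power". The result is that "the total sample size is 159 cases, with 53 cases in each group", raised to 186 (62 per group) for 15% loss. The only effect quoted is an average improvement of 0.82 mg/dL after 45 days of moderate-intensity exercise in an earlier study. Allocation is 1:1:1 to three groups (Randomized Allocation and Blinding).

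The hypotheses are pairwise and ordered. The Abstract expects both exercise arms to do better than the no-exercise control, and the Background adds that "moderate-intensity exercise is more effective than low-intensity exercise in improving HUA". The main Discussion repeats the moderate-versus-low expectation for months 6 and 12.

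Mathematical Statistics gives the between-group test for normally distributed data: "the independent sample T-test is used to judge the difference between the two groups". For other data it names the Mann-Whitney test. The rest of the list is paired t or Wilcoxon tests within groups and Spearman correlation. No test takes the three groups together.

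**The concern.** The sizing section and the analysis section describe different tests. An omnibus F test asks whether the three means differ at all. The hypotheses ask which arm beats which, and the listed tests compare two groups at a time. A power of 0.80 for the first question is not a power of 0.80 for any one of the second.

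Comparing intensities is the declared purpose of the trial, and the results are meant to inform activity guidelines. A reader who sees 80% will apply it to moderate versus low. If that comparison is not significant, the reader may conclude that intensity does not matter, when the trial may have had little chance of showing that it does.

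**Working it through.** **Inputs from the protocol article.** Power 0.80, alpha 0.05, an F test, 159 evaluable (53 per group), three groups, 1:1:1.

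**Assumptions, not in the document.** One-way omnibus form of the F test; Cohen's f = 0.25, solved back from 159; two-sided pairwise tests at 0.05; no multiplicity adjustment; mean effects ordered control ≤ low ≤ moderate.

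**Step 1: reproduce 159.** For a one-way F test with k = 3, the noncentrality is N × f², with 2 and N − 3 degrees of freedom.
- N = 156, f = 0.25: power 0.797.
- N = 159, f = 0.25: noncentrality 159 × 0.0625 = 9.94, power 0.805.

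So 159 is the first balanced total to reach 80%. Values of f from about 0.2485 to 0.251 all give 159. Because f is inferred from N, this identifies a test that fits; it does not check an effect size that the article states.

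**Step 2: translate f = 0.25 into pairwise differences.** Let the moderate-control difference be D standard deviations and the low-control difference be r × D. The standard deviation of the means 0, r, 1 is √[2(1 − r + r²)] / 3, so

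D = 0.75 / √[2(1 − r + r²)], and the moderate-low difference is (1 − r) × D.

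At r = 0.5: D = 0.75 / √1.5 = 0.612, and each adjacent difference is 0.306. At r = 0: D = 0.75 / √2 = 0.530.

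**Step 3: two-sample t power with 53 per arm.** The noncentrality is d × √(53/2). At r = 0.5 this is 0.306 × 5.148 = 1.58, and power is 34.5%.

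| Low effect as share of moderate (r) | d, moderate vs low | Moderate vs low | Low vs control | Moderate vs control |
|---|---|---|---|---|
| 0 | 0.530 | 77% | 5% | 77% |
| 0.25 | 0.441 | 61% | 12% | 85% |
| 0.4 | 0.365 | 46% | 24% | 87% |
| 0.5 | 0.306 | 34.5% | 34.5% | 88% |
| 0.6 | 0.243 | 24% | 46% | 87% |
| 0.7 | 0.179 | 15% | 57% | 86% |
| 0.75 | 0.147 | 12% | 61% | 85% |
| 1 | 0 | 5% | 77% | 77% |

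At r = 0 and r = 1 one hypothesis is false, and the 5% is the error rate.

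**Step 4: read the table.** Moderate versus low peaks at 77%, where low intensity does nothing. Whatever raises its power lowers that of low versus control. The smaller of the two adjacent differences is largest at r = 0.5, so the weaker adjacent comparison has at most about 34.5%.

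**Sensitivity.**
- With no loss (62 per arm), the r = 0.5 figure is 39.4%. Moderate versus low passes 80% only when the low effect is near zero: 83% at r = 0, 79% at r = 0.1.
- One-sided at 0.05, it is 47% at r = 0.5 and 86% at r = 0.
- With Bonferroni over three pairs, it is about 20% at r = 0.5.
- For scale only, 80% power at r = 0.5 would need about 169 per arm.

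**The case against.** **The percentages are not the sponsor's.** The article gives no f, no standard deviation, no low-intensity effect and no variant of the F test. A repeated-measures F test with four visits, an assumed correlation of 0.5 and f of about 0.198 also yields 159. This stands, and the percentages must be offered as conditional. It does not help the plan: at a single visit, f = 0.198 with equal spacing gives d = 0.198 × √6 / 2 = 0.243, and power of about 24% by the table's 0.243 row.

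**An article condenses.** Missing f, SD and assumed means may sit in the full protocol, and a three-group test may sit in an unseen analysis plan. This also stands: their absence is not the finding, and one cannot say that the F test will never be run. But the article does state both a sizing test and a list of analysis tests, and these disagree.

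**A stronger reading: that moderate versus low has at most about 34% power.** The documents do not support it. The hypotheses predict an order, not that the low effect is at least half the moderate effect. At one quarter the power is 61% with both hypotheses true. The 34.5% limit belongs to whichever adjacent comparison is weaker.

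**An arithmetic error might also be inferred.** None is shown: 159 is attainable with an F test. Nor does the article present 0.82 mg/dL as a between-arm difference.

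**Conclusion.** The point holds as a mismatch between the test used for sizing and the tests listed for analysis. The mismatch itself rests only on the article's text. Its size rests on f = 0.25 in a one-way F test, 53 per arm and unadjusted two-sided tests at 0.05.

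Under those assumptions the protocol's 80% is close to right for moderate versus control, but it is not reached for moderate versus low under any ordering that the hypotheses allow. The three hypotheses cannot all be well powered. The halfway case is an illustration; the document does not say where the low-intensity effect is expected to lie.

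**What to change.** - In Sample Size Calculation, say that the 80% applies to the omnibus F test, and give the f, standard deviation and arm means that the sponsor actually used.
- In Mathematical Statistics, add that F test ahead of the pairwise comparisons. It does not test the ordering, so this alone is not enough.
- State the power for each pairwise hypothesis, computed from the sponsor's own means and standard deviation. The 88% and 34% here illustrate f = 0.25 with equal spacing and should not be copied in as design values. Do not present 80% as the power for moderate versus low.
- Report moderate versus low as an estimated difference with a 95% confidence interval, and say that non-significance will not be read as equivalence of the two intensities.

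The cost is rewording two sections, with no extra participants. The downside is that the stated power for at least one hypothesis becomes less favourable.
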